#### General cognitive ability

3.2.2

The NIH Toolbox behavioral cognitive assessment (Weintraub et al., 2014; Mungas et al., 2014) is a series of seven cognitive batteries that will be administered on an iPad during the on-site study visit. This assessment will be used to determine individual cognitive construct assessment scores across each of the seven tasks as well as used to determine summary scores for total cognition composites. The total cognition composite scores (Heaton et al., 2014) that get computed will serve as a measure of adult general cognitive ability (GCA) in our analyses. The NIH Toolbox includes multiple cognitive tasks that will be administered and used to comprise the total cognition composite score from measures of cognitive flexibility (*Dimensional Change Card Sort*), attention (*Dimensional Change Card Sort* & *Flanker Inhibitory Control and Attention*), inhibitory control (*Flanker Inhibitory Control and Attention),* episodic memory (*Picture Sequence Memory Tests),* pattern processing speed (*Pattern Comparison Processing Speed Test),* receptive vocabulary (*Picture Vocabulary Test)*, working memory (*List Sorting Working Memory Test)*, as well as crystallized abilities and reading decoding skills (*Oral Reading Recognition).*

#### Neuroimaging

3.2.3

Participants will complete their on-site in-person session at the UCLA Staglin Center for Cognitive Neuroscience (CCN). All neuroimaging scans (structural, functional, and neurometabolic sequences) will be performed on a Siemens MAGNETOM 3T scanner (Siemens Healthcare GmbH, Erlangen, Germany) with a Nova Medical 32-channel head coil. Please see below for a summary of each type of scan sequence acquisition (see Table 1 for a summary list of all scan parameters; all sequences are described in greater detail below).

**Table 1 tbl1:** Summary overview of scan acquisitions and basic parameters.

Scan Acquisition	Voxel Size (mm^3^)	Averages	Slice #	FOV (mm)	TR/TE/TI (ms)	Flip Angle (°)	Scan Time	Scan Type
***Structural MRI***								
**T1-weighted MPRAGE**	1.0x1.0x1.0	1	208	256	1900/2.48/900	9.0	4:33	Grant
**Neuromelanin**	0.4x0.4x2.5	2	11	220	750/12/NA	120	3:44	Exploratory
***Functional MRI***								
**N-back fMRI task**	3.4x3.4x4.0	1	33	220	2000/30/NA	75	3:00/run	Grant
**Rule Switching fMRI task**	3.4x3.4x4.0	1	33	220	2000/30/NA	75	6:04	Grant
**Reward Learning fMRI task**	3.4x3.4x4.0	1	33	220	2000/30/NA	75	6:06/run	Exploratory
**Emotional Movie fMRI task**	3.4x3.4x4.0	1	33	220	2000/30/NA	75	8:00	Exploratory
**Resting-State fMRI**	3.4x3.4x4.0	1	33	220	2000/30/NA	75	7:00	Exploratory
***Neurometabolic Imaging***								
**dACC sLASER SVS MRS**	15x36x12	64	1	NA	2000/30/NA	90 excitation/180 refocusing	2:26	Grant
**L & R Hippocampus sLASER SVS MRS**	15x20x10	128	1	NA	2000/30/NA	90 excitation/180 refocusing	4:34	Grant

##### Structural magnetic resonance imaging

3.2.3.1

###### T1-weighted anatomical MRI

3.2.3.1.1

A T1-weighted magnetization-prepared rapid gradient-echo (MPRAGE) sequence will be acquired. This acquisition will be used to prescribe voxel placement to improve estimations of structural accuracy for the magnetic resonance spectroscopy (MRS) sequences, will be used during pre-processing and registration of the functional MRI (fMRI) scans, and will undergo structural processing to obtain metrics for different brain tissues. Gray matter (GM) volumes and white matter (WM) hyperintensity, which are early indicators of cognitive decline (Tondelli et al., 2012; Debette and Markus, 2010; Yamasaki et al., 2021; Raz et al., 2012), will be assessed using FreeSurfer (Knussmann et al., 2022; Fischl et al., 2002) and ENIGMA (Grasby et al., 2020) protocols to implement structural processing, extract metrics, and perform quality control procedures.

##### Task-based functional magnetic resonance imaging

3.2.3.2

###### Working memory & cognitive control task

3.2.3.2.1

The Letter N-back fMRI task will be used to assess working memory and cognitive control. This validated task demonstrates age-related differences in performance accuracy and activation of frontoparietal control networks in younger and older adults (Yaple et al., 2019), as well as between young adults who differ in terms of *ApoE* genotype (Scheller et al., 2017). This task has also been shown to differentiate between adults (without AD) who varied in terms of their reports of memory issues, suggesting that this task could be a helpful early predictor of AD. (Yeung et al., 2022) Participants will complete a blocked version of the N-back task with a cognitive load (2-back) and a control condition (0-back) (Jaeggi et al., 2010; Wang et al., 2019; Redick and Lindsey, 2013). For each block, participants will complete 20 trials, each involving seeing a letter presented for 1500 ms with a jittered interstimulus interval. On 0-back (control) trials, participants are instructed to press a key with their index finger whenever they view the letter “X.” On 2-back trials (high working memory load), participants are instructed to press with their index finger whenever they see a letter that matches the letter they viewed two trials ago. Participants are instructed to press with their middle finger for all “non-match” trials. There are 60 trials per condition across three runs of this game, with each run lasting 3 min.

###### Cognitive flexibility task

3.2.3.2.2

We will assess cognitive flexibility by administering the Rule Switching fMRI task, which differentially recruits frontostriatal networks across age in young adulthood (Rubia et al., 2006). This task leverages a rapid, mixed trial, random presentation, event-related design and is 6 min and 4 s long (152 total trials with jittered ITI). Participants will view a 2x2 grid with a double headed arrow positioned either horizontally or vertically at the center of the grid. On each trial, a red dot will appear in one of the squares of the grid and participants are instructed to respond about whether the red dot is on the right or left of the grid if the arrow is positioned horizontally, and whether the red dot appears in the top or bottom of the grid if the arrow is positioned vertically. Switch trials (when the rules change) are randomly dispersed after four, five, or six repeat trials (when the rule stays the same).

##### Neurometabolic imaging

3.2.3.3

###### Magnetic resonance spectroscopy (MRS)

3.2.3.3.1

Neurometabolic data will be characterized with single voxel (SV) magnetic resonance spectroscopy (MRS) in three different regions: dorsal anterior cingulate cortex (dACC), right hippocampus, and left hippocampus. The dACC was chosen as a region of interest because of its involvement in cognitive control and it has been previously implicated in MRS studies assessing metabolic alterations in those with mild cognitive impairment and AD. (Huang et al., 2017; Chen et al., 2025) The hippocampus was chosen as a region of interest given that it is a critical region for learning and memory and it has been shown to be a sensitive and central region for AD, particularly for disease pathology, early disease diagnosis, as well as for disease progression (Song et al., 2021). Additionally, prior MRS studies have observed significant metabolite alterations in the hippocampus in AD patients compared to controls, including metabolites that are indicators of neuroinflammation (Song et al., 2021). In line with MRS expert consensus (Wilson et al., 2019) for data acquisition at 3T *in vivo*, we will implement a short echo time semi-LASER (sLASER) sequence (Oz and Tkáč, 2011; Deelchand et al., 2021) to be used with an automated B_0_ and B_1_ shimming calibration protocol (Gruetter and Tkác, 2000; Deelchand et al., 2022) to improve acquisition of high-quality MRS data. LCModel (Provencher, 2009) will be used to fit and quantify all estimated metabolite concentrations with total creatine acting as an internal reference standard. Quality assurance procedures include ensuring all metabolite estimations that will be used for analysis have relative Cramer-Rao lower bounds (CRLBs) < 25%. GM and WM tissue percentages will also be calculated within each voxel to correct for total tissue content.

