## Power analysis

4

We conducted a power analysis where tests of hypothesized differences were performed using linear contrast analysis within the framework of random effects general linear models (GLMs). For these single degree of freedom tests, power was approximated using two-tailed independent sample *t*-test in G∗Power 3.1.9.7. For the moderator analysis examining sex-specific associations between education opportunity and the primary outcome, brain health, at an alpha .05/2 markers of brain health = .025, 150 participants per group (mobile/static 1:1 ratio female:male) provided adequate power (80%) to detect an effect size difference as small as Cohen's d = 0.36 (tcrit = 2.25, noncentrality parameter = 3.10), if it exists. This sample size also provided 80% power to detect associations as little as f^2^ = .04 (multivariate linear regression for moderated mediation analyses, Crit F = 2.24, noncentrality parameter = 13.07).

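### The MRS inclusion rule (relative CRLB below 25%), read as a filter on single estimates, removes low values and can shrink mobility and sex contrasts for metabolites fitted near that limit

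*Protocol article*

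**What the plan says.** Section 3.2.3.3.1 of the protocol article describes single-voxel spectroscopy in the dorsal anterior cingulate and both hippocampi, fitted in LCModel "with total creatine acting as an internal reference standard". Among the quality assurance procedures it lists one numerical criterion, that "all metabolite estimations that will be used for analysis have relative Cramer-Rao lower bounds (CRLBs) < 25" percent. It then adds that "GM and WM tissue percentages will also be calculated within each voxel to correct for total tissue content".

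Table 1 labels these acquisitions as grant scans rather than exploratory ones. Section 2 (H1 and H4) predicts worse brain health in females with mobility opportunity; H1 predicts better brain health in males with it. The article names no target metabolites, no expected CRLB values and no expected share of estimates failing the limit.

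**The concern.** A quality filter should depend on how good the spectrum is, not on how large the answer is. Relative CRLB depends on both, because the estimate is its denominator. Two participants with equally good spectra and the same absolute uncertainty can be treated differently only because one has the lower concentration.

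The group with the lower true mean then loses more values, and those it loses are its lowest. The retained means move toward each other. This happens whether mobility lowers a metabolite (the mobility group loses more) or raises it (the comparison group loses more). Since H1 predicts opposite directions in females and males, the sex-by-mobility contrast would be attenuated too. The loss is not the random kind that only costs precision: it biases the estimate toward no difference.

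**Working it through.** **The plan's own figure.** The Power analysis section works "at an alpha .05/2 markers of brain health = .025", two-tailed, with 150 per group and d = 0.36. The noncentrality is 0.36 × √(150/2) = 3.12, the critical t on 298 df is 2.25 and power is 80.6%. The stated noncentrality of 3.10 corresponds to d = 3.10/√75 = 0.358. The stated 80% reproduces and is not disputed.

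**What the rule means.** Let m be the estimate and s its absolute CRLB. Then s/m < 0.25 is the same as m > 4s, which is a lower cut on the outcome.

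**Inputs (assumed; the article gives none).** Means 1.0 and 0.9, so a true difference of 0.10; between-person SD 0.15; median absolute CRLB from 0.05 to 0.25, which is a typical relative CRLB of 5% to 25% at mean 1.0.

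**Simplest case, fixed CRLB and no fit noise.** The mean of the retained values is μ + σ·φ(α)/(1 − Φ(α)), with α = (4s − μ)/σ. For s = 0.20 the cutoff is 0.80.
- Higher group: α = (0.80 − 1.0)/0.15 = −1.33; 9% dropped; retained mean 1.027.
- Lower group: α = (0.80 − 0.9)/0.15 = −0.67; 25% dropped; retained mean 0.964.
- Retained difference: 1.027 − 0.964 = 0.063, against a true 0.10.

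**Range of cases.** Case A is as above. Case B lets CRLB vary between people (lognormal, log-SD 0.2). Case C adds to B fit noise with SD equal to the CRLB. B and C were simulated with 2 million values per group. Entries are the retained difference, then the percentage dropped in the higher / lower group.

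| Typical relative CRLB | A | B | C |
|---|---|---|---|
| 5% | 0.100 (0/0) | 0.100 (0/0) | 0.100 (0/0) |
| 10% | 0.100 (0/0) | 0.099 (0/0.3) | 0.097 (0.3/1) |
| 15% | 0.093 (0.4/2) | 0.091 (3/7) | 0.082 (7/12) |
| 20% | 0.063 (9/25) | 0.078 (20/34) | 0.066 (26/37) |
| 25% | 0.030 (50/75) | 0.071 (51/67) | 0.053 (49/61) |

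Fit noise without CRLB spread gives 0.081 at 15% and 0.033 at 25%. A wider spread (log-SD 0.4) weakens the effect at the limit, because more exclusions then reflect poor spectra: 0.087 without fit noise and 0.078 with it, at 25%. In every case the lower group loses at least as many values as the higher, and strictly more wherever the rule excludes an appreciable share.

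**Where it would bite.** From Table 1, the cingulate voxel is 15 × 36 × 12 mm = 6.48 mL with 64 averages, and each hippocampal voxel is 15 × 20 × 10 mm = 3.0 mL with 128. Taking signal as volume × √averages, the ratio is (6.48 × 8)/(3.0 × 11.3) = 1.53. On these figures alone, relative CRLB would be higher in the hippocampus, so the filter would act more often there.

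**The case against.** **The rule may not be a per-estimate filter.** The article presents the CRLB limit as one of the quality procedures, not as the complete list, and does not say whether a failure removes one participant's value or the whole metabolite. That is fair. The absence of linewidth or signal-to-noise criteria from a condensed article is no defect, and a cohort-level reading would largely meet the point. But the wording attaches the limit to the estimates used for analysis, and the per-estimate reading is the more natural one.

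**The effect may be nil.** For metabolites fitted at 5% to 10%, it is. This stands, and it limits the point to metabolites near the limit.

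**Not every failing value is a low outcome.** The analysed quantity is a ratio to creatine. Values that fail because of a poor spectrum, or because CSF dilutes metabolite and creatine alike, are not low ratios. This also stands. It reduces the attenuation, as the wider CRLB spread shows, but does not remove it.

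**Two stronger readings the documents do not support.** A reader might infer that the study is underpowered. The Power analysis section does not say that spectroscopy is one of its two brain-health markers, and Section 2 describes worse brain health under H4 as reduced prefrontal activation. A reader might also infer that creatine ratios will be over-corrected by dividing them again by the tissue fraction. The article never states the form of the tissue correction. A covariate for gray-matter share would be defensible and is compatible with the sentence. No error is shown there.

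**Conclusion.** The point holds in a conditional form. As worded, the rule selects on the outcome, and wherever it excludes an appreciable share of estimates it pulls group differences toward zero. Under the assumed means and SD, a true difference of 0.10 remains 0.097 to 0.100 at a typical relative CRLB of 10% or less (log-SD of CRLB up to 0.2; about 0.095 with a log-SD of 0.4). With a log-SD up to 0.2, it falls to about 0.08 to 0.09 at 15% and to about 0.03 to 0.07 at 25%. The direction follows from the definition of relative CRLB at equal spectral quality. The size rests on assumptions, because the article gives neither the metabolites nor their expected CRLBs. No stated power or sample-size figure is affected, and the tissue correction is not part of the finding. Because the scans serve the grant aims and only wording needs to change, it is worth settling before the data are analysed.

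**What to change.** Use the CRLB limit once, on the pooled cohort (for example the median CRLB for each metabolite and region), to decide which metabolites are analysed. For those metabolites, keep every participant's estimate. Reject an individual spectrum only on criteria that do not depend on concentration: linewidth, signal-to-noise, visible artefact, or an absolute CRLB limit. Report the number rejected by mobility group and sex, so that any imbalance can be seen.

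The cost is a change in analysis wording, with no change to scanning. The downside is that some noisier values remain and slightly widen the intervals.

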#### Additional measures for exploratory analyses on emotion and reward

3.2.4

Emotion processing dysfunction (i.e., facial and social emotion processing) and disturbance (Chaudhary et al., 2022; Spoletini et al., 2008; Weiss et al., 2008; Jiskoot et al., 2021; Stam et al., 2023), have been previously associated with AD, with emotion recognition deficits manifesting at earlier stages in the course of AD. (Chaudhary et al., 2022) Preliminary evidence has also shown evidence for reward processing deficits in AD. (Perry and Kramer, 2015) Importantly, anxiety and depression can manifest at various stages of AD (Botto et al., 2022), but are often early behavioral symptoms and signs of AD related dementia development (Alzheimer's disease facts and figures, 2024; Botto et al., 2022). Thus, assessing emotion and reward related processing may be particularly important for early detection of AD related dementia. As such, this study protocol will include multiple exploratory indices of neural and behavioral measures of emotion and reward processing (described in this section). Half of the participants in this cohort (N = 150) will be randomly assigned to complete the additional emotion processing tasks (emotional movie fMRI task and faces behavioral task) and the other half will be randomly assigned to complete the additional reward related tasks (reward learning fMRI task and post-scan reward memory task). We will also aim to collect neuromelanin and resting state functional imaging on as many participants as possible as part of the scan protocol if time allows. Please see below for additional exploratory imaging protocols.

##### Additional task-based functional magnetic resonance imaging

3.2.4.1

###### Reward learning task

3.2.4.1.1

150 participants will be randomly assigned to complete the reward learning fMRI task (Esfand et al., 2024), adapted from existing reward learning paradigms that successfully engage frontostriatal regions (Calabro et al., 2023; Parr et al., 2021), inside the scanner to assess reward-related brain activation and connectivity. This task has two phases: the first is the reward learning phase which is completed during the fMRI task inside of the scanner and the second is the reward spatial memory phase which is completed as a post-scan computer task. Participants will complete two 6 min and 6 s runs (36 trials per run) with the same sequence parameters as the task-based functional imaging in Table 1.

In brief, during the reward learning phase, participants will explore a 3x3 grid map by choosing different locations on the map to move a penguin to find potential hidden rewards. For each trial, participants have two options of where they can move their penguin; these options are first depicted as “#”s (2-6s) that are then replaced by a “1” or “2”. The participant will have a brief amount of time (2s) to select either location 1 with their index finger or location 2 with their middle finger to move and display the penguin in the new location on the map (2s). If they do not select a location, they will be automatically moved to location 1. Next, the trial outcome will be displayed (2s) for the participant to receive feedback: no reward (blank), small reward (one gold coin; 75% of rewards), or a large reward (multiple stacked gold coins; 25% of rewards). Each map location will have a set reward probability (25%, 50%, or 75%) while each option presented to move to will always differ in their likelihood of reward (see Esfand et al., 2024 for task design figures).

After the scan, participants will complete the reward spatial memory task to assess how much they learned. This computer task consists of 27 trials with no performance feedback. Participants will be shown the same 3x3 grid map but will now indicate which of the two map location options (indicated with a “1” or “2” on the computer) were associated with a greater probability of rewards (i.e., their goal will be to choose the location with the larger reward outcome) (Esfand et al., 2024). Following their location selection, a “∗” will be shown to confirm their selection choice (2s).

###### Emotional movie task

3.2.4.1.2

150 participants will be randomly assigned to complete the emotional movie task that will present participants with a brief suspenseful clip from the “Bang! You're Dead” episode of the “Alfred Hitchcock Presents” television series (1961). The adapted movie clip shown to participants in the scanner is an 8 min condensed compilation of the original 25 min episode that still preserves the episode's essential plot narrative and has been successfully used in previous research studies (Shafto et al., 2014; Geerligs and Campbell, 2018; Keles et al., 2024; Taylor et al., 2017; Kliemann et al., 2022; Sun et al., 2022). During the scan, participants will be instructed to watch, listen and continuously (sampled at ∼ 10 Hz) report their subjective experience of emotional intensity while viewing the video. The rating of intensity will not have bounds: the reported ratings can increase or decrease without limit. Participants will indicate increases (more) or decreases (less) in intensity using two buttons that allow the subjective intensity rating line at the bottom of the screen to change throughout the movie. Participants will not be aware of the movie title prior to viewing it and will be asked after viewing the movie if they have seen this movie previously. This 8 min scan will have the same sequence parameters as the task-based functional imaging presented in Table 1.

##### Additional structural magnetic resonance imaging

3.2.4.2

###### Neuromelanin

3.2.4.2.1

We will collect a T1-weighted Fast Spin Echo sequence to estimate levels of neuromelanin, a byproduct of norepinephrine metabolism (Clewett et al., 2016) and a proxy measure of dopamine (Wakamatsu et al., 2015; Horga et al., 2021), in dopaminergic and noradrenergic rich brain regions including the substantia nigra and the locus coeruleus—important regions that show neurochemical changes in response to emotional stress (Tanaka et al., 2000), are important for cognitive processing (Clewett et al., 2016; Sara, 2009; Caestecker et al., 2025), and are affected by AD brain pathology early (Caestecker et al., 2025; Beardmore et al., 2021) which may contribute to early anxiety and depression symptoms (Iannitelli et al., 2023). This sequence will utilize the following parameters: TR = 750ms; TE = 12.0ms; FA = 120°; FOV = 220mm; Slice thickness = 2.5mm; Voxel size = 0.4x0.4x2.5mm^3^; Scan time = 3 min 44 s (see Table 1). The FOV will be manually aligned to be centered on the locus coeruleus prior to collecting.

##### Resting-state functional magnetic resonance imaging

3.2.4.3

###### Resting-state

3.2.4.3.1

We will collect resting-state fMRI to assess whole brain functional organization and connectivity with the same imaging parameters as the task-based functional imaging in Table 1. Participants will be instructed to remain awake and stare at a fixation cross on the screen during the 7 min sequence.

##### Behavioral tasks

3.2.4.4

